To derive a ‘real-world’ dataset from all patients available to RITeS, and simultaneously maximise sample size, we will therefore: 1) Include all structural stroke mimics for e-ASPECTS testing (since this will be far less than 26%, but see planned sensitivity analyses for our primary outcomes below)2)For the remainder of included patients (i.e. non-mimics), aim for sex and age mix, stroke severity and time since symptom onset similar to SSNAP, pooled thrombolysis/ thrombectomy RCT data, and haemorrhagic stroke registry data.3)Not exclude imaging based on quality.

The most recent SSNAP annual dataset (Apr 2018-Mar 2019) identified 87,635 patients presenting acutely with stroke and had 93% data completion. Of these patients, 47.8% were female, median age was 77 years, 87.1% of strokes were ischaemic, 12.4% were haemorrhagic (0.4% unknown), and the median NIHSS was 5. For 69.4% of patients, the time of symptom onset was known and the median time from stroke onset to baseline scan in these patients was 4 hours and 2 minutes^30^. A pooled analysis of nine thrombolysis RCTs by the Stroke Thrombolysis Trialists’ Collaborative (STTC) group included 6,756 patients of whom 45% were female, the mean age was 71 years, the mean NIHSS was 12, and the mean treatment delay was 4 hours^25^. A pooled analysis of seven thrombectomy RCTs by the Highly Effective Reperfusion evaluated in Multiple Endovascular Stroke Trials (HERMES) collaboration included 1764 patients of whom 47% were female, the median age was 67 years, the median NIHSS was 17, and the mean time from onset to randomisation was 3 hours^4^. A comprehensive, community-based audit of haemorrhagic stroke in Scotland (The Lothian Audit of the Treatment of Cerebral Haemorrhage, LATCH) included 137 patients with primary haemorrhagic stroke of whom 55% were female, the median age was 79 years, and the median Glasgow Coma Scale at presentation was 13^31^,^32^.

To ascertain the representativeness of the non-mimic cases within the RITeS dataset, we will report demographic and clinical data as per SSNAP, STTC, HERMES and LATCH data (see Table 2). We will report absolute differences, 95% confidence intervals and p-values for comparisons. We will also present continuous data components using overlapping histograms.

To ascertain the representativeness of relevant radiological features in RITeS, we will also report the features listed in Table 3.

**
*Sample for e-CTA evaluation.*

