### Sample size considerations

Tests of diagnostic accuracy are difficult to power and benefit from maximising the sample size^33^. In addition, sample size calculations may be inappropriate in this setting^34^. We therefore aim for the largest representative sample possible within available resources. However, to allow direct comparison with previous work, we estimated that to confirm that e-ASPECTS software is non-inferior for an “MCC (Matthews Correlation Coefficient) better than random” (to expert human calculation of ASPECTS using an MR diffusion-weighted imaging reference standard: e-ASPECTS correlation 0.44 versus 0.38 for experts), based on 34 patients^35^, requires a sample size of 494 scans – at 5% non-inferiority limit with 80% power and at 5% significance level. Therefore, we have set the minimum sample size for our primary outcome at 500 unique patient CT brain scans. Up to 31% of scans may fail to give an e-ASPECTS result for technical reasons^36^, therefore we will inflate the minimum sample to 725 scans (i.e. 1/0.69 × 500) to ensure the successfully processed sub-sample includes the requisite minimum 500 scans. However, this minimum will have limited power for subgroup analyses (e.g. on pre-stroke brain changes, by age or stroke severity strata) and the study cited for our power calculation used individual ASPECTS regions rather than individual patients to power their analysis, which due to lack of independence between individual ASPECTS regions, may be flawed^35^. Therefore we will process every available scan to derive the largest possible sample for testing.

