
### Primary outcomes

For these evaluations of e-ASPECTS, we will use a representative RITeS sample of NECT.

In two analyses, we will compare e-ASPECTS results to those provided by expert human readers for the assessment of non-enhanced brain CT acquired at baseline among patients presenting acutely with symptoms of stroke.

**
*Representative sampling for e-ASPECTS testing of primary outcomes.*
** Where clinical or demographic features are different to the comparator SSNAP/STTC/HERMES datasets (i.e. RITeS values should be within the range provided by the other datasets), we will use stratified random sampling to remove select cases (which are over-representing these features) to reduce these differences while maintaining the maximum sample size from the data available to RITeS. For example, if RITeS has 42% female patients and a median NIHSS of 19, we would identify all male patients with a high NIHSS and randomly remove subsets of these until the sex ratio and NIHSS are within the desired ranges. We will not select cases on the basis of the radiological features in Table 3.

To assess the impact of factors beyond our control which might affect the representativeness of our sample, we will perform sensitivity analyses of our primary outcomes for the following randomly selected subgroups: 1. With balanced representation from all RITeS trials, i.e. we will exclude surplus cases for trials which are relatively over-represented (more than double the median trial contribution).2. Where non-stroke mimics represent 26% of the total sample.

**
*1. Difference in ASPECT scores of e-ASPECTS and expert human readers.*
** We will compare e-ASPECTS and expert human results using overlapping histograms and Mann-Whitney U testing to assess the distribution of results, and Wilcoxon signed rank testing and Bland-Altman plots to assess pairwise agreement for each case. For results to be considered equivalent on Bland-Altman testing, we expect the range of agreement to be within ± 2 ASPECTS points. This is an arbitrarily derived but clinically meaningful difference that might lead to alterations in treatment for individual patients based on the thresholds presented below. We will also use K-alpha statistics to assess software-human reader agreement for these scalar data.

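### The 26%-mimic sensitivity analysis can be formed only by deleting non-mimics; weighting the full representative sample answers the same question with less sampling error

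*SAP article*

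**What the plan says.** In the SAP article, the section on inclusion and exclusion criteria (sample for e-ASPECTS evaluation) takes in all structural mimics, "since this will be far less than 26%, but see planned sensitivity analyses for our primary outcomes below". The 26% is the mimic share that the plan reports from RIGHT-2.

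Under Statistical analysis, Primary outcomes (representative sampling), the plan states: "we will perform sensitivity analyses of our primary outcomes for the following randomly selected subgroups". The second of these is: "Where non-stroke mimics represent 26% of the total sample". In context this means stroke mimics at 26%, although Table 2 uses almost the same phrase for cases that are not mimics.

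The plan gives no mimic count. For this subgroup it gives no method of reaching 26%, no number of draws and no weighting. Under Sample size considerations it says: "we have set the minimum sample size for our primary outcome at 500 unique patient CT brain scans".

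**The concern.** A subgroup of a sample that already holds every mimic can reach 26% mimics in only one way, by dropping non-mimics at random. If mimics are scarce, most of the stroke scans go. A comparison with the main result then mixes two things: the real effect of a higher mimic share, and the noise from having discarded much of the data.

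This matters because it is the plan's only stated check on the under-representation of mimics, and the plan itself notes that sensitivity and specificity may vary with prevalence. A difference produced by the draw could be read as a mimic effect, or could hide one.

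**Working it through.** **Inputs from the plan.** Target share 26%; all structural mimics already included; minimum of 500 scans for the primary outcome; 6612 patients (sum of the Table 1 patient column), of whom 5128 are in the ischaemic studies (6612 − 947 − 537). **Assumed:** the mimic share, 1% to 10%.

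**The plan's own figure.** "requires a sample size of 494 scans – at 5% non-inferiority limit with 80% power and at 5% significance level". Treating the two MCC values, 0.38 and 0.44, as proportions, with a margin of 0.05 and one-sided 5%: (1.645 + 0.842)² × (0.38 × 0.62 + 0.44 × 0.56) / (0.06 + 0.05)² gives 247 per group, and 2 × 247 = 494. This reproduces. So does the inflation, 500/0.69 = 725.

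**Subgroup size.** With *m* mimics, all kept, N = *m*/0.26. For N = 500, *m* = 0.26 × 500 = 130. That is 2.0% of 6612 or 2.5% of 5128. For 725 scans, *m* = 189.

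**Non-mimics kept.** At mimic share *p*, the fraction kept is (0.74/0.26) × *p*/(1 − *p*). The standard error of ischaemia sensitivity, which is estimated among non-mimics, grows by 1/√(fraction kept).

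**Deletion against weighting for overall accuracy at 26% mimics.** Assumed accuracies are 60% for ischaemia, 90% for haemorrhage and 50% for mimics, with haemorrhage 12.4% of non-mimics. Non-mimic accuracy is then 0.876 × 0.60 + 0.124 × 0.90 = 0.637. With *k* non-mimics used, the variance is 0.26² × 0.25/*m* + 0.74² × 0.637 × 0.363/*k* = 0.0169/*m* + 0.1266/*k*. Deletion has *k* = *m* × 0.74/0.26; weighting has *k* = *m*(1 − *p*)/*p*. The ratio of interval widths is the square root of (0.0169 + 0.0445)/(0.0169 + 0.1266 × *p*/(1 − *p*)).

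| Mimic share (assumed) | Mimics, of 6612 | Subgroup size | Non-mimics kept | SE of ischaemia sensitivity | Accuracy interval, deletion ÷ weighting |
|---|---|---|---|---|---|
| 1% | 66 | 253 | 2.9% | × 5.9 | 1.84 |
| 2% | 132 | 507 | 5.8% | × 4.1 | 1.77 |
| 5% | 331 | 1273 | 15% | × 2.6 | 1.61 |
| 10% | 661 | 2542 | 32% | × 1.8 | 1.41 |

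As absolute 95% half-widths with 6612 scans:
- 103 mimics: deletion uses 293 non-mimics and gives 4.8 points; weighting uses 6509 and gives 2.7.
- 331 mimics: deletion uses 942 and gives 2.7 points; weighting uses 6281 and gives 1.7.

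**Which measures respond.** A simulation with 3000 non-mimics, 66 mimics and illustrative detection rates compared the full sample with the 26% subgroup:
- Ischaemia sensitivity: 0.600 and 0.600, with the SD rising from 0.009 to 0.039.
- Ischaemia specificity: 0.828 to 0.740.
- Ischaemia PPV: 0.952 to 0.807.
- Ischaemia MCC: 0.306 to 0.326.
- Sensitivity for any structural cause: 0.646 to 0.578.
- Haemorrhage sensitivity: 0.900 and 0.898 if no mimic is a haemorrhage, but 0.875 to 0.693 if 40% of mimics are.

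The last case is relevant because the tertiary haemorrhage section counts subdural and subarachnoid haemorrhages among the scans classed as mimics in the ischaemic trials.

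**The case against.** The strongest defence is that random deletion is unbiased for what it sets out to estimate, that this is a supporting analysis, and that the plan's 95% intervals would make any loss of precision visible. That stands as far as it goes: no primary result changes. It does not answer why a less precise estimator should be used when a better one needs no new data.

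Four stronger readings are tempting, and the documents do not support them.

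- *The subgroup breaches the 500-scan minimum.* That minimum is set for the primary outcome, and nothing applies it to sensitivity analyses. It is a benchmark here. Whether the subgroup falls short also depends on an unstated count: 5% mimics would give 1273 scans. The allowance of up to 31% processing failures is an upper figure, and primary testing is by intention to analyse.
- *More than 90% of stroke scans are discarded.* This holds only if mimics are below about 3.4% of the sample (0.10 × 0.26/0.74 = 0.035 for *p*/(1 − *p*)).
- *Several primary measures can yield only noise.* Ischaemia sensitivity is the one clear case. Haemorrhage sensitivity can shift, because some mimics are haemorrhages. Any other case depends on coding that the plan does not state.
- *Only one draw will be made.* The plan does not give the number.

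It is also fair to say that the representative sample will be smaller than 6612. Since every mimic stays in, the subgroup size is unaffected, but the mimic share rises. The table's last three columns depend only on that share.

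**Conclusion.** The concern holds as a point about construction, not purpose. That non-mimics must be deleted, and that N = mimics/0.26, follow from the plan's own text. At any mimic share below 26%, weighting targets the same quantities with smaller variance. Over assumed shares of 1% to 10%, deletion keeps about 3% to 32% of non-mimics and makes the accuracy interval about 1.8 to 1.4 times as wide as weighting does. The width figures rest on the assumed accuracies, the retained fractions only on the assumed share. For ischaemia sensitivity the subgroup carries no information about the mimic share. The change is worth making because it is cheap and this is the plan's only stated check on a 26% share.

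**What to change.** Replace the second sensitivity analysis with a weighted analysis of the whole representative sample:

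- Give each mimic the weight 0.26/(observed mimic share) and each non-mimic 0.74/(observed non-mimic share), with bootstrap or robust intervals.
- Where a method does not take weights easily, average the result over many repeated random draws, and state the number of draws.
- Report the number of structural mimics, and say plainly that stroke mimics are the group set to 26%.
- State that ischaemia sensitivity is not expected to change with the mimic share.
- Re-estimate haemorrhage sensitivity along with specificity, predictive values, accuracy, MCC and sensitivity for any structural cause.

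The cost is SAP wording, a few lines of code and slightly more analysis work, with no new data. For this sensitivity analysis, robust or bootstrap intervals would replace the Wilson intervals used elsewhere.

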We will classify e-ASPECTS and expert-human scores into three groups to assess diagnostic accuracy at the following clinically relevant cut-points, and present a summary (receiver-operating characteristic) ROC curve: 1) ASPECTS 10 (normal) versus ASPECTS 0-9 (abnormal)2) ASPECTS 0-7 versus 8-10^2^.3) ASPECTS 0-5 versus ASPECTS 6-10^4^.

To compare with previous work, we will use Matthews correlation coefficient (MCC), and test non-inferiority between e-ASPECTS and expert-human scores^5^,^35^. We will calculate MCC as (TPxTN)-(FPxFN)/√(TP+FP)(TP+FN)(TN+FP)(TN+FN)^46^. We will set our non-inferiority margin at 5%. Thus using the two one-sided test (TOST) procedure, we will establish non-inferiority, using the following formula: at the α=5% significance level, if the lower limit of a (1-2α) × 100% (i.e. 90%) confidence interval for the difference (e-ASPECTS minus expert-human results) is above -5%. The confidence interval is set at (1-2α) rather than the usual (1-α) because the method is equivalent to performing two one-sided tests^47^,^48^.

**
*2. Accuracy of e-ASPECTS versus expert human readers for identifying cause of stroke symptoms.*
** We will compare the diagnostic accuracy of e-ASPECTS software and expert human readers (at baseline, blind to all other clinical data including further imaging) for three groups against the reference standard, human-expert opinion using all available follow-up data including further imaging: 1) Identifying features of ischaemic stroke (including ischaemic lesions in any brain location and/or intracranial hyperattenuating arteries)2) Identifying haemorrhage, and3) Identifying any structural causes of stroke symptoms on baseline imaging (including mimics).

In addition, to aid clinical understanding and real-world applicability, we will summarise all primary outcome results using normalised frequencies. Thus we will present results as proportions of 1000 individual patients, i.e. a test sensitivity of 90% would be presented as: the test will detect disease in 900 of 1000 patients with the disease, but 100 patients with the disease will be missed by the test^49^.

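### The MCC analysis is justified as a direct comparison with earlier work, but unit and reference standard appear to differ, so a RITeS MCC cannot be read against 0.44 or 0.38

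*SAP article*

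**What the plan says.** Sample size considerations bases its calculation on MCC "to allow direct comparison with previous work". The inputs are "e-ASPECTS correlation 0.44 versus 0.38 for experts", from a study "based on 34 patients" and "using an MR diffusion-weighted imaging reference standard". The calculation is made "at 5% non-inferiority limit with 80% power and at 5% significance level" and gives 494 scans, rounded up to a minimum of 500 scans from different patients. The same section then notes that the cited study "used individual ASPECTS regions rather than individual patients to power their analysis". It treats this as a possible flaw because regions within a patient are not independent, and responds by processing every available scan.

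Under Statistical analysis, Primary outcomes, item 1, the total ASPECTS is split at three cut-points: 10 versus 0-9, 0-7 versus 8-10, and 0-5 versus 6-10. The next paragraph introduces the MCC test: "To compare with previous work, we will use Matthews correlation coefficient (MCC), and test non-inferiority between e-ASPECTS and expert-human scores". The margin there is 5%, presented as the authors' own choice. Neither the unit nor the cut-point that supplies the counts for MCC is named.

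Analysis principles and general considerations makes expert human results the reference from which true and false positives and negatives are counted.

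**The concern.** Comparison with earlier work is the only reason given for using MCC. That reason holds only if the two MCCs estimate the same quantity. An MCC over regions asks whether the reader marks the right regions. An MCC over dichotomised totals asks whether the reader puts the patient on the right side of a threshold. A reader can do well on one and poorly on the other: errors in different regions may cancel in the total, and one wrong region is enough to misclassify a truly normal scan at the cut 10 versus 0-9.

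If the comparison is reported as planned, a RITeS MCC away from 0.44 or 0.38 may be taken as a change in the performance of software or experts when the unit, the cut-point or the reference has produced it. The plan sees the regional unit only as a problem of independence for power. Processing more scans improves precision but does not turn a regional MCC into a patient-level one.

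**Working it through.** **1. The plan's own figure.** Inputs from Sample size considerations: 0.38 (experts), 0.44 (software), margin 0.05, power 80%, significance 5% (taken as one-sided).

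Treating the two MCCs as proportions in two independent groups:

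n per group = (z₀.₉₅ + z₀.₈₀)² × [0.38 × 0.62 + 0.44 × 0.56] / (0.44 − 0.38 + 0.05)²

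= 6.1826 × (0.2356 + 0.2464) / 0.0121 = 246.3, so 247 per group and 2 × 247 = 494 in total.

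This matches the stated 494 exactly. The inflation also reproduces: 500 / 0.69 = 724.6, so 725. Values from region-based work were therefore entered into a calculation counted in scans.

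**2. The two MCCs side by side.**

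| | Earlier study, as the SAP describes it | RITeS, natural reading of the SAP |
|---|---|---|
| Unit | Individual ASPECTS region (stated for its power analysis) | Patient scan: the sample is counted in patients, and the MCC paragraph follows cut-points of the total score |
| Split | Not stated | One of three cut-points; which one is not stated |
| Reference | Diffusion-weighted MRI | Expert human reading |

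No region-by-region ASPECTS comparison is planned. Where regions are wanted the plan says so, as for the 22 haemorrhage regions (Tertiary outcomes, item 1, and Table 8).

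**3. Size of the unit effect.** The documents do not give the inputs for this step, so all are assumptions.

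*Set A.* 24 scenarios of 100,000 patients with 10 regions; region prevalence 0.15 or 0.30; within-patient correlation 0.2 or 0.5; regional sensitivity/specificity of 0.45/0.92, 0.55/0.85 or 0.60/0.85; correlation of reader errors within a patient 0 or 0.3. Region-level MCC was 0.35-0.46. For the same readers at patient level:

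| Cut-point | Patient-level MCC | Patient minus region | Shift above 0.05 |
|---|---|---|---|
| 10 vs 0-9 | 0.20-0.37 | −0.23 to −0.06 | 24 of 24 |
| 0-7 vs 8-10 | 0.23-0.53 | −0.15 to +0.09 | 12 of 24 |
| 0-5 vs 6-10 | 0.16-0.54 | −0.22 to +0.10 | 21 of 24 |

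In all, 57 of 72 shifts exceed 0.05 (47 downwards, 10 upwards), using MCCs rounded to two decimals.

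*Set B.* 60,000 patients per scenario, every reader tuned to a region-level MCC of 0.44; region involvement 20-31%; 10 or 20 regions; varying correlation within patients and within readers. Patient-level MCC was 0.30-0.42, 0.35-0.66 and 0.33-0.70 at the three cut-points.

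The ranges of the two sets differ. What they share is that the unit alone can move MCC in either direction, often by more than 0.05. The earlier software-expert difference was 0.44 − 0.38 = 0.06.

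**4. The reference standard.** If the experts' readings are the reference, their own counts have FP = FN = 0, so

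MCC = (TP × TN) / √(TP × TP × TN × TN) = 1.

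The planned difference, software minus expert, is then the software MCC minus 1. A software MCC of 0.44 would give −0.56, and a lower limit above −0.05 would need a software MCC above 0.95. The contrast is informative only with a reference separate from the readings being compared.

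**The case against.** Several points on the other side are sound.

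- The unit of the RITeS MCC is inferred. Patient level is the natural reading, but the plan does not say so. If the unit is in fact open, the same correction, to state it, is needed.
- That 0.44 and 0.38 are themselves regional is also inferred, from the remark about how that study was powered. The MCC paragraph cites two sources as earlier work, and the plan describes the unit of only one.
- A reader might infer that the mismatch biases the non-inferiority test. It does not. The test takes software minus expert within RITeS, both on the same unit, and no rule judges the result against 0.44 or 0.38.
- A reader might infer that the 5% margin was borrowed from the earlier study. The plan presents it as its own. The supportable criticism is that no reason is given for 5% on the MCC actually used.
- The simulated ranges depend on assumed inputs and do not predict the RITeS values.
- MCC is one of several analyses. Diagnostic accuracy is the principal method, alongside Bland-Altman, Wilcoxon and Krippendorff's alpha. The plan also doubts the value of sample size calculations in this setting and processes all scans.

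These points limit the consequence. They do not rescue the stated purpose: a direct comparison is claimed, and on the plan's own description the conditions for it are not met.

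**Conclusion.** The concern holds in a limited form. The plan claims comparability for its MCC that the design, as described, does not provide: unit and reference standard both appear to differ from the study supplying 0.44 and 0.38, and the cut-point is not fixed. A RITeS MCC should not be read as better or worse than those figures. On assumed inputs the unit alone shifts MCC by −0.23 to +0.10 in one set of simulations. Only the finding that shifts go in either direction and often exceed 0.05 should be relied on.

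The conclusion assumes that the RITeS MCC is patient-level and that the earlier MCCs are regional. Both are strong inferences rather than stated facts. It does not extend to bias in the internal comparison of software with experts. That comparison has a separate problem: if the general rule on the reference standard applies to it, the experts' MCC equals 1 by construction.

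**What to change.** Before un-blinding:

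1. In Primary outcomes, item 1, state the unit, the cut-point and the reference standard for MCC. The reference must be separate from the expert readings being compared.
2. For a patient-level MCC, remove the claim of direct comparison from Sample size considerations and the comparison purpose from the MCC paragraph.
3. Compare with 0.44 and 0.38 only through a region-level MCC, with a 90% interval from a bootstrap that resamples patients, and only in cases where regional scores and a matching reference are held. A region-level MCC against a different reference would still not be comparable.
4. Justify the 5% margin for the MCC actually used, or report the MCC difference with its interval and make no non-inferiority claim.
5. Say in Sample size considerations that 494 comes from treating two MCCs from region-based work as independent proportions counted in scans.

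The cost is mainly SAP wording, plus one extra analysis if regional scores and a matching reference exist. If they do not, the sponsor loses the comparison with earlier work.
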